### Measures

#### Study Outcomes

We will ask participants to self-report the following demographic characteristics: age, gender, sexuality, ethnicity, employment, education, marital status, household income, and postcode (to calculate the index of multiple deprivation). The following list of self-report questionnaires is then administered throughout the study (Table 2). We sought to use measures consistent with the original Australian FMW study to most closely replicate this previous clinical trial. Exceptions include (1) a briefer measure was identified to reduce participant burden (eg, using the Psychological Impact of Cancer Scale [37] rather than the mini-Mental Adjustment to Cancer Scale [38]); (2) an additional measure was required to assess psychological flexibility, our hypothesized mediator of the intervention effect; and (3) a UK-specific measure of health resource use was needed for context-specific health economic assessment.

**Table 2 table2:** Schedule of questionnaire administration.

Variable	Baseline assessment	Midpoint assessment	Beginning of sixth module	End of Finding My Way UK	3-month follow-up	6-month follow-up
Demographic characteristics	✓^a^					
Cancer-specific distress (Post-Traumatic Stress Scale)	✓	✓		✓	✓	✓
Psychological well-being (Depression, Anxiety, and Stress Scales 21-item version)	✓	✓		✓	✓	✓
Quality of life (QLQ-C30^b^)	✓	✓		✓	✓	✓
Psychological adjustment to cancer (the Psychological Impact of Cancer Scale)	✓	✓		✓	✓	✓
Health care use (the UK Cancer Costs Questionnaire)	✓	✓		✓	✓	✓
Perceived social support (the Medical Outcome Study Social Support Survey)	✓					
Emotion regulation (Difficulties in Emotion Regulation Scale)	✓					
Information-seeking preferences (the Miller Behavioral Style Scale)	✓					
Psychological flexibility (the CompACT Questionnaire)	✓	✓		✓	✓	✓
Engagement with intervention (Self-Help Compliance Scale)			✓			

^a^Assessment performed.

^b^QLQ-C30: European Organisation for Research and Treatment of Cancer Quality of Life Core Questionnaire.

#### Primary Outcome

The primary trial outcome variable was cancer-specific distress*.* For this variable, we will use the Post-Traumatic Stress Scale [39], a 17-item measure in which participants respond on a 4-point Likert scale, where responses are anchored from 0 (*not at all or only one time*) to 3 (*5 or more times per week or almost always*). The Post-Traumatic Stress Scale is associated with excellent internal consistency reliability (α=.91) [39] and has good concurrent validity, including strong positive correlations with other measures of trauma-related intrusion and avoidance, anxiety, and depression [39]. Higher scores on the Post-Traumatic Stress Scale indicate a greater severity of cancer-specific distress.

#### Secondary Outcomes

##### Psychological Well-being

The Depression, Anxiety, and Stress Scales, 21-item version [40] is a short measure of negative emotions experienced over the course of the past week for the individual. Each item is scored on a 4-point Likert scale, anchored from 0 (*did not apply to me at all*) to 3 (*applied to me very much or most of the time*). Total scores for each subscale of the Depression, Anxiety, and Stress Scales, 21-item version can be calculated, where higher scores indicate greater levels of depression, anxiety, and stress. The scale has good internal reliability (depression, α=.91; anxiety, α=.81; stress, α=.89), and concurrent validity, including strong positive correlations with other measures of depressive symptoms and anxiety [40].

##### Quality of Life

The European Organisation for Research and Treatment of Cancer Quality of Life Core Questionnaire (QLQ-C30) [41] is a 30-item quality of life assessment for cancer patients, which yields a global quality of life score and five functional subscale scores associated with physical, emotional, social, role, and cognitive quality of life domains. In total, 28 items are presented on a 4-point Likert scale ranging from 1 (*not at all*) to 4 (*very much*). The final two items assessing subjective assessment of overall health and quality of life are presented on a 7-point Likert scale anchored from 1 (*very poor*) to 7 (*excellent*). The global score for the QLQ-C30 is associated with good internal consistency reliability (α=.86) and has good concurrent validity, with both global quality of life and domain subscales significantly positively correlated with performance status throughout treatment [41]. A higher global score on the QLQ-C30 indicates a greater quality of life. The QLQ-C30 score can be converted into an indication of Quality-Adjusted Life Years for use in health economic analysis.

##### Psychological Impact of Cancer

The Psychological Impact of Cancer Scale [37] is a 12-item self-report measure of psychological adjustment to cancer. Each item is presented on a 4-point Likert scale anchored from 1 (*definitely does not apply to me*) to 4 (*definitely applied to me*). The Psychological Impact of Cancer Scale yields four subscale scores: cognitive distress, cognitive avoidance, emotional distress, and fighting spirit. Greater scores on each subscale indicate greater levels of the named construct (eg, a greater score on the Cognitive Distress subscale indicates greater levels of cognitive distress). The fighting spirit subscale will not be included because of underlying psychometric property issues [37]; the remaining three scales have reasonable internal consistency reliability (α≥.62) and good concurrent validity with longer measures of psychological adjustment to cancer [37].

##### The UK Cancer Costs Questionnaire

The UK Cancer Costs Questionnaire [42] is a flexible modular self-report measure of resource use by people with cancer and those with a previous diagnosis of cancer. The UK Cancer Costs Questionnaire assesses employment status, family support provided, government benefits received, and support provided by other organizations over the previous 3 months. The UK Cancer Costs Questionnaire prioritizes brevity to minimize the burden of data collection for participants. For full health care use outcome data, this self-report questionnaire is supplemented by health service resource use data extracted from clinical records and the calculation of Quality-Adjusted Life Years from the QLQ-C30.

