### Procedure

After reading information provided by the CRN RNs, patients wishing to take part in the study can access our study recruitment website via a link in their information pack. This provides a full trial information sheet and access to a web-based consent form. Once their consent is submitted, participants are redirected immediately to the baseline survey via the *Qualtrics survey platform* (Qualtrics). Participants also will receive an automated email with a link to complete the baseline questionnaire at a later date or in a number of sittings if they prefer*.* Upon full completion of the baseline questionnaire, an unblinded member of the research team will complete the study arm allocation using a computerized randomization allocation system using *REDCap* software (Vanderbilt University) [36]. The randomization algorithm was set up to ensure equal numbers of participants in both the intervention and control arms, stratified by cancer diagnosis to ensure the spread of patients across both trial arms. The randomization system was set up and is overseen by the Liverpool Clinical Trials Centre. Following allocation, participants are either emailed account details to access the FMW UK website (intervention group) or sent a PDF copy of a site-specific information pack listing existing local and national sources of psychosocial support that they can access as part of treatment as usual (control group; Figure 1). Control participants also have the option to receive a hard copy of the information pack via the post.

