At the point of being informed of intervention allocation, automated email reminders to complete the study questionnaires are set up through *Qualtrics*. Text messages or phone call reminders (as preferred) are sent for a period of 7 days without submission of any specific questionnaire. Questionnaires are completed at the end of the third (midintervention) and sixth (posttreatment) week, and then at 3- and 6-month follow-ups, both timed from the release of the posttreatment questionnaire. Participants are sent a debrief sheet at this point, and control arm participants are granted access to the FMW UK website. At this point, CRN RNs complete clinical data extraction from hospital records using a standard form; this includes information about the date of diagnosis, primary or recurrent diagnosis, curative or palliative treatment intent, principle treatment approach adopted (surgery, chemotherapy, radiotherapy, or watch-and-wait), date of the end of active treatment (if applicable), date of any recurrence or relapse (if applicable), date of death (if applicable), known referrals to mental health care teams since diagnosis, number of days of inpatient care since study enrollment and types of health care professionals seen during these stays, the number of outpatient visits since study enrollment and types of health care professionals seen during these visits, and any diagnostic tests conducted since study enrollment. As this study is registered on the UK NIHR CRN Portfolio, costs for most CRN RN activities (both recruitment and clinical data collection) are covered by CRN Study Support Services, with costs for additional archiving at each site reimbursed by the clinical trial research grant.

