### Analysis

The analysis plan matches the Australian FMW RCT [27] as closely as possible. Members of the research team involved in the analysis will be blinded to the condition allocation until the end of the trial. First, we will conduct data cleaning to ensure that all data values are possible and plausible. Errant data entries will be deleted from the final analysis data set and missing data will be handled using either prorating or imputation methods as is (1) appropriate to the collected data and (2) congruent with the specific scoring instructions for the psychometric measure from which there is a missing response.

Descriptive statistics will be used to provide sample characteristic information and to identify any potentially prognostic demographic or clinical covariates. Inferential statistical analyses are powered to undertake mixed model repeated measures analyses to examine intervention effects on change from baseline to follow-up for each outcome, using intention-to-treat analysis. Two models will be run for each: (1) unadjusted, accounting for covariance of baseline measures of outcomes and (2) fully adjusted, controlling for all potential confounding variables assessed. Where possible and adequately powered, we will include potential confounders in our analyses and evaluate the effects of missing data using sensitivity analysis. Cohen *d* effect sizes reflect intervention effects, and clinically significant changes will be assessed using reliable change indices. The health care use outcome will be summarized descriptively for activity counts and cumulative costs estimated by assigning unit costs to units of activity. Cost summaries are derived from discrete payer perspectives. Generalized linear models will be used to adjust for the same confounding variables as in the efficacy analysis. All quantitative data analyses will be undertaken in R software (R Foundation for Statistical Computing) [50] where possible, with any supplementary analyses conducted in IBM SPSS as appropriate*.*

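### The cost questionnaire's 3-month recall does not fit its use at baseline, week 3 and week 6, so self-reported use in weeks 0-6 cannot be isolated

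*Protocol article*

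**What the plan says.** The section on the UK Cancer Costs Questionnaire gives the recall: it covers employment, help from family, "government benefits received, and support provided by other organizations over the previous 3 months". It calls the instrument flexible and modular but states no shorter recall for any visit.

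In Table 2 (Study Outcomes), the row beginning "Health care use (the UK Cancer Costs Questionnaire" is ticked at baseline, midpoint, end of programme, 3 months and 6 months. The Procedure section fixes the times: "Questionnaires are completed at the end of the third (midintervention) and sixth (posttreatment) week, and then at 3- and 6-month follow-ups", the last two "both timed from the release of the posttreatment questionnaire". Randomisation comes after the baseline form: "Upon full completion of the baseline questionnaire, an unblinded member of the research team will complete the study arm allocation".

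The questionnaire is "supplemented by health service resource use data extracted from clinical records". Those records are extracted once, at the end of follow-up, and are counted from enrolment, for example "number of days of inpatient care since study enrollment"; outpatient visits and diagnostic tests are treated the same way.

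The Analysis section plans descriptive activity counts, with "cumulative costs estimated by assigning unit costs to units of activity". It gives no rule for combining the questionnaire's successive windows.

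**The concern.** A recall period should match the gap between administrations. Here a 13-week look-back is used at visits three weeks apart, straight after randomisation. The early forms therefore mix use that the intervention could affect with use that it could not, and they overlap each other and the baseline form.

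Health economic outcomes are named beside distress and quality of life in the Abstract, and the Discussion makes lower health care use one of the things the trial will test. The items at risk are those for which the article names no other source: employment, family support, benefits and support from other organisations. The mismatch arises when the data are collected, so a later analysis rule can limit the damage but cannot recover what was not asked.

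**Working it through.** The article gives no figure of its own to reproduce, so the check is interval arithmetic.

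**Inputs.** Recall: 3 months (questionnaire section), taken as 13 weeks. Forms: Table 2. Times: week 0 is the baseline form and randomisation, then weeks 3 and 6, then 6 + 13 = 19 and 19 + 13 = 32 (Procedure). A form at week t covers weeks t - 13 to t.

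| Form | Weeks covered | Weeks before randomisation |
|---|---|---|
| Baseline | -13 to 0 | 13 of 13 |
| Week 3 | -10 to 3 | 10 of 13 (77%) |
| Week 6 | -7 to 6 | 7 of 13 (54%) |
| 3-month follow-up | 6 to 19 | 0 |
| 6-month follow-up | 19 to 32 | 0 |

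**Can weeks 0-6 be isolated?** Split the time into a = (-13, -10), b = (-10, -7), c = (-7, 0), d = (0, 3) and e = (3, 6). The first three forms report a + b + c, b + c + d and c + d + e. The target is d + e. In any weighted sum of the three forms, removing a needs weight 0 on the baseline form, removing b then needs weight 0 on the week-3 form, and removing c needs weight 0 on the week-6 form. Nothing is left, so no combination gives d + e. The follow-up forms start at week 6 and do not help. Prorating would work only under an assumed constant rate of use.

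**What plain addition would do (self-reported items only).**
- Weeks recalled by the four post-baseline forms: 4 × 13 = 52. True follow-up: 32.
- Pre-randomisation: 10 + 7 = 17 weeks (17/52 = 33%).
- Post-randomisation: 52 - 17 = 35, which is 32 distinct weeks plus weeks 0-3 a second time.
- Inflation at constant weekly cost: 52/32 = 1.63.
- A true 10% saving would show as 10% × 35/52 = 6.7%. If weekly cost before randomisation were twice that after (assumption), it would show as 10% × 35/(2 × 17 + 35) = 3.5/69 = 5.1%.
- Absolute difference between arms: the 17 earlier weeks cancel in expectation, leaving 35 weeks of effect where there should be 32. A constant weekly effect is overstated by 35/32 - 1 = 9%.

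**Sensitivity.** With 3 months taken as 12 weeks, the early forms are 75% and 50% pre-randomisation, 15 earlier weeks are counted, and the inflation is 48/30 = 1.60. The conclusion does not depend on the rounding.

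**After the change.** Windows 0-3, 3-6, 6-19 and 19-32 cover 32 weeks once each.

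**The case against.** The strongest reply is that the article never says the forms are added. A cost error needs both an unchanged 3-month wording at weeks 3 and 6 and plain summation. A flexible, modular instrument could have been given a shorter recall, and the full protocol, which the article says is openly available but which is not shown here, may settle both points. This stands as a limit on the claim. A reader might infer that the trial's cumulative costs do count pre-randomisation months; the article does not support that as a fact. The reply does not remove the mismatch, because the only recall the article states conflicts with the schedule it states, even if nothing is summed.

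Second, the main hospital items come from records counted since enrolment, which neither reach back nor double-count. This also stands. A reader might apply the 1.6-fold inflation to total cost, but it applies only to self-reported items. If these made up 20% of true cost (assumption; the article gives no share), a true 10% saving in total cost would show as (8 + 2 × 35/32)/(80 + 20 × 52/32) = 10.19/112.5 = 9.1%, not 6.7%. Some items, such as employment status, are states and would not naturally be added across forms.

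Third, randomisation balances earlier use in expectation. That is right, so the absolute difference is not diluted. What remains is noise, a diluted relative difference, and double weight on weeks 0-3.

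One might also hope that the record extraction could fill in weeks 0-6. As described it cannot: it gives totals since enrolment, not dated visits, and it does not cover employment, family support, benefits or support from other organisations.

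**Conclusion.** The point holds as a mismatch between a stated recall and a stated schedule. As written, 77% of the week-3 window and 54% of the week-6 window lie before randomisation, and self-reported use in weeks 0-6 cannot be isolated. This rests only on the article's recall and visit times, with 3 months taken as 12 to 13 weeks and week 0 as randomisation.

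The cost consequence is conditional. If the post-baseline forms are added with that recall, self-reported totals count 17 pre-randomisation weeks and weeks 0-3 twice, and are about 1.6 times too large at constant weekly cost. Relative differences shrink, and the absolute difference gives weeks 0-3 double weight. Hospital-record data are untouched. The effect on total cost depends on the self-reported share, which the article does not give. The outcome is secondary and the remedy is cheap, so this should be changed, but it does not threaten the primary analysis.

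**What to change.** Set the recall to 'since your last questionnaire' at weeks 3 and 6, or drop the questionnaire at week 3 and ask 'since you joined the study' at week 6. Keep 3 months at the two follow-ups. Define cumulative self-reported cost as weeks 0-6 plus 6-19 plus 19-32.

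For participants already assessed with the 3-month wording, leave the week-3 and week-6 forms out of the self-reported total and report it for weeks 6-32. Take hospital costs from the record extraction since enrolment, and state that the two sources then cover different periods. If the full protocol already sets a shorter recall at the two early visits, correct the article's description instead.

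The cost is a wording change in two web forms and one sentence in the analysis plan. The downsides are small: a departure from the standard recall at two visits, and loss of self-reported use in weeks 0-6 for early participants.

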#### Potential Intervention Moderator or Mediators

##### Rationale for Moderator and Mediator Analyses

In psychological intervention research, it is important to include measures of the hypothesized variables being acted upon to (1) verify cause-and-effect relationships on outcome improvements and (2) identify any important moderator and mediator analyses that may need to be undertaken [13]. The following measures were identified as likely moderators of the effectiveness of the intervention and have been informed in large part by a moderator analysis of the Australian FMW Trial [43].

##### Perceived Social Support

The Medical Outcome Study (MOS) Social Support survey [44] is a 20-item measure, with items presented as a 5-point Likert scale anchored from 1 (*none of the time*) to 5 (*all of the time*). The MOS Social Support Survey yields four subscale scores: emotional or informational support, tangible support, affectionate support, and positive social interactions. Each subscale is associated with excellent internal consistency reliability (α>.91) [44]. The MOS Social Support Survey is associated with good convergent validity with measures of family ties, family functioning, and mental health, and good divergent validity with measures of purely physical health [44]. Higher scores on individual subscales and the overall support index indicate greater social support.

##### Emotion Regulation

The Difficulties in Emotion Regulation Scale [45] is a 36-item self-report measure of six dimensions of emotion regulation difficulties: lack of awareness of emotional responses, lack of clarity of emotional responses, nonacceptance of emotional responses, limited access to emotion regulation strategies perceived as effective, difficulties controlling impulses when experiencing negative emotions, and difficulties engaging in goal-directed behaviors when experiencing negative emotions. Each item is scored on a 5-point Likert scale ranging from 1 (*almost never*) to 5 (*almost always*). The global difficulties in emotional regulation scale is associated with excellent internal consistency reliability (α=.93), and each subscale is associated with good internal consistency reliability (α>.80) [45]. The Difficulties in Emotion Regulation Scale is associated with good construct validity and predictive validity [45]. Higher scores on the Difficulties in Emotion Regulation Scale indicate greater problems with emotion regulation.

##### Information-Seeking Preferences

The Miller Behavioral Style Scale [46] is a self-report measure of information-seeking preferences. The scale identifies individual preferences for seeking threat-related cues (monitors) versus seeking distraction to minimize exposure to threat-related cues (blunters). The scale prompts participants to imagine four stressful scenarios, each of which is followed by eight statements that describe different ways of coping with the stressor. Participants are asked to select all the statements that apply to them. The Miller Behavioral Style Scale is associated with good test-retest reliability over a 4-month period (monitoring subscale *r*=0.72; blunting subscale *r*=0.75) and high construct validity, as indicated by high correspondence with information-seeking behavior in a stress-inducing laboratory task [46]. Higher scores on the Miller Behavioral Style Scale indicate greater tendencies for monitoring information-seeking preference, rather than blunting information-seeking preference.

##### Self-help Compliance

The Self-Help Compliance Scale [47] is a brief measure assessing engagement with self-guided psychological interventions. The scale consists of 3 items presented on a 5-point Likert-type scale assessing the amount of information participants read (anchored from *0%* to *100%*), the number of suggestions and worksheets participants completed (anchored from *0%* to *100%*), and how much time participants spent using the program per week (anchored from *None* to *61+ minutes*). The questionnaire also includes one open question asking participants what other psychological treatment they had received during the program.

We also predict that psychological flexibility will mediate the effect of the UK-adapted FMW intervention. We operationalized psychological flexibility using CompACT [48].

